### Data collection, management, and monitoring

Data from demographic interviews, EEG recordings, cognitive tests, and self-report measures will be collected for all participants. The time points of data collection are shown in Table 1. The participants’ names and contact information will be in an initial form that the principal investigator will keep. Afterward, each participant will be known by a unique numeric identifier, and all data will be stored with that ID. Once a participant completes an assessment session, the data will be transferred to a secure digital database. The database will include EEG records, output files of computerized tests, demographic data that are digitalized manually, and the outputs of self-report measures. The online self-reports will contain a unique ID with no additional personal information. The trial management group (TMG) convenes every week and the trial steering committee (TSC) meets every month to review the implementation of the trial. The TMG is responsible for managing and overseeing the daily operations and activities of the trial. They are responsible for ensuring that the trial is conducted efficiently and effectively. The TSC, consisting of a psychiatrist, a psychologist, a neuroscientist, and a medical engineer, approves TMG actions and provides advice. In addition, they provide reports for the ethics committee and funders. A data monitoring committee (DMC) also meets every six months during the trial, as the trial is considered a low-risk intervention. This committee monitors the completeness of informed consents, data safety, and correspondence with the ethics committee. In case of interim results, the DMC decide to terminate the trial.

### Statistical analysis

First, data entry will be double-checked. Data quality will be examined regarding data distribution, and outliers will be excluded from further analysis. When these items are ensured, the primary and secondary outcomes will be analyzed in detail using IBM SPSS statistics 25 for Windows (Armonk, NY: IBM Corp). Descriptive statistics (e.g., mean and standard deviation) will be reported for each arm separately. We will conduct the analysis within the intention-to-treat (ITT) framework to investigate the effectiveness of the interventions for all subjects with multiple imputed data sets in case of missing data. The appropriate statistical method will be performed to analyze data. The major one will include mixed and repeated measures of multivariate analysis of variance (MANOVA) to assess the effect of group (arm) and time and their interactions on the result of EEG recordings, computerized tests, and self-report measures as dependent variables. The significant level will be set at 0.05. The covariates, including age, disgust sensitivity, anxiety, and depression, will be considered in the statistical model.

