### Sample size

We calculated the sample size using the G*Power 3.1 software. To be able to get an effect on our primary outcomes (disgust feeling and clinical symptoms) in three measurements (pre-, post-, and follow-up) at repeated-measure-MANOVA approach, with 95% confidence and 80% power, estimating large effect size with Cohen’s *f* value 0.40, a sample size of 46 participants was calculated. With an attrition rate of 20%, we aim to enroll 55 participants.

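### Excluding outliers before the primary analysis contradicts the promised intention-to-treat analysis of all subjects and allows valid extreme scores to be deleted

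*Protocol article*

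**What the plan says.** The Statistical analysis section of the protocol article sets out its steps in order. Data entry is checked twice. Then comes the outlier step: "Data quality will be examined regarding data distribution, and outliers will be excluded from further analysis". The next sentence fixes its place and scope: "When these items are ensured, the primary and secondary outcomes will be analyzed in detail". The exclusion therefore comes first and covers the primary outcomes.

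The same paragraph then states: "We will conduct the analysis within the intention-to-treat (ITT) framework to investigate the effectiveness of the interventions for all subjects with multiple imputed data sets", with imputation reserved for data that are missing. The main method is "mixed and repeated measures of multivariate analysis of variance (MANOVA) to assess the effect of group (arm) and time and their interactions", and "The significant level will be set at 0.05".

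Under Expected outcomes, the primary outcomes are disgust, measured on the Disgust Rating Scale (DRS), and clinical symptoms, measured by PI-WSUR and Y-BOCS. Under Randomization and blinding, the design is single-blind and only participants are described as blind. The article does not say who judges outliers or whether that person sees the arm.

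**The concern.** Intention-to-treat means that each randomised patient is analysed as assigned, using the outcomes observed. Removing a score because it lies far from the others is a post-randomisation exclusion that depends on the outcome itself. It can act differently between arms, because a working treatment is what produces unusually large changes.

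Two things are at stake. The first is bias: patients who respond strongly, or not at all, can be taken out of the comparison meant to detect them. The second is the error rate: trimming within arms shrinks the residual variance, and an unspecified rule leaves room to choose one after the results are known.

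**Working it through.** **1. The two statements side by side.** Entry errors are dealt with in a separate, earlier step, so the outlier step does something more; its stated criterion is the distribution of the data. Multiple imputation does not reconcile it with intention-to-treat. If a flagged score is deleted and imputed, the patient stays in, but an observed outcome is replaced by a prediction. It is also missing precisely because of its own value.

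**2. The scales.** From Self-report measures: DRS ratings run 0 to 10; Y-BOCS has ten items scored 0 to 4 (total 0 to 40); PI-WSUR has 39 items scored 0 to 4 (total 0 to 156). A range check finds impossible values. A value that passes it may be genuine.

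**3. Arm size, from the plan's own figure.** The Sample size section assumes "with 95% confidence and 80% power" and "estimating large effect size with Cohen’s *f* value 0.40", with three measurements and 46 patients. For the group-by-time interaction (Pillai, k = 4 arms, p = 2 contrasts, s = 2):
- df1 = 3 × 2 = 6
- df2 = s(N − k − p + s) = 2(46 − 4 − 2 + 2) = 84
- λ = N·s·f² = 46 × 2 × 0.16 = 14.72
- power = 0.802

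The 46 is reproduced. Per arm: 46/4 = 11.5; after 20% loss from 55, 44/4 = 11; as enrolled, 55/4 = 13.75. Arms of 11 and 13 were simulated.

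**4. Type I error of the planned test.** Assumptions, none from the article: 20,000 trials with no effect, three visits correlated 0.5, normal data or strongly skewed data (exponential of 0.8 times a normal). A patient is dropped if any screened value is flagged. Screening is on the raw scores at the three visits or on the change scores. The test is Pillai group-by-time at 0.05. Entries are 11 / 13 per arm.

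| Rule | Normal, raw | Normal, change | Skewed, raw | Skewed, change |
|---|---|---|---|---|
| None | 0.048 / 0.046 | 0.048 / 0.046 | 0.034 / 0.036 | 0.034 / 0.036 |
| Pooled 2 SD | 0.046 / 0.047 | 0.045 / 0.048 | 0.041 / 0.044 | 0.042 / 0.044 |
| Pooled 1.5 IQR | 0.047 / 0.046 | 0.045 / 0.048 | 0.042 / 0.043 | 0.044 / 0.044 |
| Pooled 3 SD | 0.048 / 0.046 | 0.047 / 0.046 | 0.042 / 0.043 | 0.042 / 0.042 |
| Within-arm 2 SD | 0.079 / 0.081 | 0.119 / 0.132 | 0.087 / 0.090 | 0.090 / 0.093 |
| Within-arm 1.5 IQR | 0.063 / 0.061 | 0.086 / 0.078 | 0.109 / 0.120 | 0.103 / 0.109 |

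A within-arm 3 SD rule has almost no effect at 11 per arm: the largest possible standardised deviation in 11 values is (n − 1)/√n = 10/√11 = 3.015.

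**5. Rule chosen after seeing results.** Taking the lowest p-value among the rules tried, at 11 per arm with heavy-tailed, moderately skewed and lognormal scores, gave 0.146, 0.164 and 0.194 for a one-way ANOVA on a single score. For a 2 × 2 main effect it gave 0.128, 0.142 and 0.162. Hence 0.13 to 0.19, for single-score tests. A recheck on the group-by-time test, with the settings of step 4 and the lowest p-value over no exclusion and 2 SD, 1.5 IQR and 3 SD rules (within arm and pooled), gave about 0.10 to 0.17. The order of magnitude is the same.

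**6. What a pooled rule does to a true effect.** Assume 2 of 11 patients in one arm respond by 3 SD and everyone else is null. With everyone kept, the expected difference is 2/11 × 3 = 0.55 SD. After pooled 2 SD or 1.5 IQR exclusion it is about 0.10 to 0.22 SD. After within-arm exclusion it is roughly 0.3 to 0.4 SD.

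**The case against.** The best defence is that this is routine data-quality work. It stands next to the entry check and also covers reaction times and EEG, where trimming is normal. The cut-off belongs in an analysis plan, and the wording permits deletion of valid scores without showing that it will happen. The last two points stand, and the absence of a cut-off is not the complaint. But the article itself fixes the exclusion and applies it to the primary outcomes; an analysis plan could only define the threshold.

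A reader might also draw four stronger conclusions that the document does not support:
- **That the plan doubles the false-positive rate.** This needs a tight within-arm rule, and then only in some settings, or a rule chosen after the results. The article states neither. Judging outliers on the pooled sample is at least as natural a reading, and it causes no inflation. Even the within-arm 1.5 IQR figure depends on the quartile convention: 0.083 to 0.113 for a one-way F test on normal data.
- **That small arms are the cause.** Arms of 13 give about the same inflation as arms of 11.
- **That unblinded staff decide who is excluded.** The article does not say who does this. What can be said is that no masking of the step is stated.
- **That one flagged value removes the whole patient.** The article does not say whether values or patients are excluded, and it provides for multiple imputation. The simulations drop whole patients by assumption.

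**Conclusion.** The sentence is wrong as written. Exclusion on the basis of observed outcome values and an intention-to-treat analysis of all subjects cannot both describe the primary analysis. This conclusion rests on the text alone and needs no simulation.

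The numerical consequence is conditional. It ranges from none (pooled rules, or 3 SD within arms of 11) to type I error of up to about 0.13 on the planned test under tight within-arm rules, and more if the rule is chosen afterwards. These figures rest on assumed distributions, a visit correlation of 0.5 and assumed rules. The rules that leave type I error alone are not thereby harmless: tight pooled rules can remove most of an effect carried by a few strong responders. Skewness gives no reason to exclude, since keeping everyone holds the planned test at or below 0.05 in the settings tried.

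**What to change.** Replace the outlier sentence with: *No participant or valid primary-outcome score is excluded for being extreme; only verified data errors are corrected.* Move any outlier rule for the primary scales to a sensitivity analysis, with the cut-off and the pooled or within-arm basis fixed in advance and the rule applied with arm codes masked.

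The cost is one sentence, plus masked arm codes for whoever runs the sensitivity analysis. The downside is slightly wider intervals if a real extreme score occurs. No change to the sample size is needed.

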**Method:**

In a single-blind randomized control trial (RCT), 55 patients with contamination-based OCD will be randomly assigned to four arms. In a factorial design, they will receive 10 sessions of evaluative conditioning training (either sham or real) plus cathodal transcranial direct current stimulation (tDCS) over the orbitofrontal cortex (either sham or real). The intensity of disgust experience and clinical symptoms will be investigated as primary outcomes and quantitative electroencephalogram and cognitive functions as secondary outcomes. The data will be collected at three assessment levels: baseline, after completing intervention sessions, and 2-month follow-up.

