OCD pathophysiology shares neurocircuits and brain structures involved in disgust processing [29]. Among them are the insular cortex and orbitofrontal cortex (OFC). Insular activity is a neural correlate for disgust processing [30, 31]. Insula shows regular higher activity in experiencing actual disgusting stimuli, but the abnormality is when an OCD patient confronts a symptom-provoking stimulus that is not genuinely disgusting. In this situation, insular hyperactivity showed that non-disgusting stimuli are mistakenly perceived as highly disgusting [32]. The insula sends some projections to the OFC [33, 34], the area engaged in coding the aversive value of the stimuli [35], and its enhanced activity, among the insula and other areas, is associated with avoidance behavior in a disgust-relevant situation [36]. The OFC also showed increased gray matter volume in people with higher disgust sensitivity (how much they are distressed when experiencing disgust) [37]. Neuroimaging studies reported the overactivation of OFC in OCD patients [38]. The neuromodulation techniques in this area, such as transcranial direct current stimulation (tDCS), have a therapeutic effect on OCD symptoms [39, 40].

The present study aims to design an EC training targeting disgust toward contamination-related stimuli in C-OCD patients. The hypothesis is that pairing such stimuli with pleasant USs may decline the disgust evoked. The proposed intervention will target lings of disgust more directly and precisely. We will also investigate the effect of brain stimulation over the OFC on disgust processing in C-OCD people. Finally, we are interested in whether adding this neuromodulation technique to the EC training may boost the EC effect. So, we will compare the effectiveness of individual and combined interventions in reducing disgust reactivity.

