## Methods/design

### Study design and setting

This study is a four-arm, randomized, placebo-controlled clinical trial in which participants get sham or real forms of two interventions, including EC and tDCS. It is aimed to investigate the effectiveness of EC, tDCS, and a combination of both on disgust reduction, clinical symptoms, and cognitive characteristics in C-OCD patients. Randomly assignment will be in blocks of 4 in 1:1:1:1 allocation to four parallel groups: (1) real EC plus real tDCS, (2) sham EC plus real tDCS, (3) real EC plus sham tDCS, (4) sham EC plus sham tDCS. We consider sham interventions to be able to separate the exposure effect from the EC effect and also to monitor the placebo effect. Assessments occur at baseline, after completion of 10 interventional sessions, and in a 2-month follow-up. All groups have similar assessments and equal intervention amounts (equal time, activity, and number of sessions). Figure 1 shows the design of the study. The trial will be conducted in the Cognitive Science Laboratory of Ferdowsi University of Mashhad, Mashhad, Iran.

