**Table 1 Tab1:**
[figure not shown]
Procedure schedule

*EC*, evaluative conditioning, *tDCS*, transcranial direct current stimulation, *EEG*, electroencephalography, *DPT*, dot-probe test, *EGNT*, Emotional Go/NoGo test, *ESST*, Emotional Stop-Signal test, *PI-WSUR*, Padua Inventory-Washington State University Revision, *Y-BOCS*, Yale-Brown Obsessive-Compulsive Scale, *DS-R*, Disgust Scale-Revised, *BDI-II*, Beck Depression Inventory-II, *BAI*, Beck Anxiety Inventory, *DRS*, Disgust Rating Scale

The primary outcome measures will be disgust reduction and change in clinical symptoms. We hypothesize that pairing C-OCD-related stimuli with positive USs can reduce disgust feeling toward them in C-OCD patients, and simultaneously cathodal tDCS over left OFC may boost this effect. For that, we will measure the amount of disgust elicited by contaminated stimuli on a Disgust Rating Scale, at baseline and after completing interventions. We will also look for possible transfer effects in OCD symptoms from pre- to post-interventions, measured via PI-WSUR and Y-BOCS. Based on previous studies in which the role of disgust has been implied in the pathology of OCD and the assumption that targeting this negative emotion may have treatment outcomes, it is hypothesized that EC may lead to diminishing C-OCD symptoms, mainly when it is along with cathodal tDCS, over left OFC.

The secondary outcomes include cognitive measures and QEEG recording. Disgust as a negative emotion may affect cognitive functions [61, 62], and OCD patient has been shown to have cognitive deficits in attention, memory, and executive function [63–65]. First, we aim to examine attentional bias and inhibitory control in C-OCD patients when confronted with contaminated stimuli compared with neutral ones. Then, the study will explore whether entering these contaminated stimuli into a positive EC training leads to better performance in these cognitive tests. We are also interested in investigating the correlation of cognitive performance level with the self-reported disgust rating, both at the baseline and after completing interventions. For QEEG recording, we will look for changes in brain wave characteristics from pre- to post-interventions.

We expect a more significant effect for all measures when the EC training is combined with cathodal tDCS than each one alone. We will also detect hypothesized effects at a 2-month follow-up.

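### A 2x2 factorial trial is analysed, and apparently sized, by one four-arm by time test that does not separate the EC, tDCS and boost effects

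*Protocol article*

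**What the plan says.** The Abstract (Method) calls the design factorial: "In a factorial design, they will receive 10 sessions of evaluative conditioning training (either sham or real", combined with real or sham tDCS. Study design and setting confirms the full crossing: "Randomly assignment will be in blocks of 4 in 1:1:1:1 allocation to four parallel groups". Arm 1 is real EC with real tDCS, arm 2 sham EC with real tDCS, arm 3 real EC with sham tDCS, and arm 4 both sham.

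Background asks three questions:
- EC: "The hypothesis is that pairing such stimuli with pleasant USs may decline the disgust evoked".
- tDCS: "We will also investigate the effect of brain stimulation over the OFC on disgust processing in C-OCD people".
- Boost: "whether adding this neuromodulation technique to the EC training may boost the EC effect".

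Expected outcomes adds an expectation about single arms: "We expect a more significant effect for all measures when the EC training is combined with cathodal tDCS than each one alone".

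Statistical analysis opens with a general statement, "The appropriate statistical method will be performed to analyze data", and then names mixed and repeated-measures MANOVA as the major method, "to assess the effect of group (arm) and time and their interactions on the result of EEG recordings, computerized tests, and self-report measures". It names no EC factor, tDCS factor, EC x tDCS term or contrast between arms.

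Sample size gives a repeated-measures MANOVA with three measurements, Cohen's f of 0.40, 80% power and 95% confidence. The result is 46, raised to 55 for 20% attrition. It states neither the number of groups nor the effect that is powered.

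**The concern.** With four arms and three visits, the arm by time interaction has 3 x 2 = 6 degrees of freedom. It tests whether the arms differ in any way in their course over time. EC alone, tDCS alone, both without synergy, or a change in the combined arm only can each make it significant. The conclusions the trial wants to draw concern those patterns separately.

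Two things are at stake. First, a significant result of the stated major analysis would not by itself support a statement about EC, tDCS or a boost. Second, a reader of Sample size may take the 80% to cover each hypothesis, when it appears to cover only the omnibus test.

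**Working it through.** **1. Reproducing the stated 46.** Inputs from Sample size and Study design and setting: 4 groups, 3 visits, f = 0.40 read as G*Power's f(V), alpha 0.05. For the repeated-measures MANOVA within-between interaction, s = min(3, 2) = 2, df1 = 6, df2 = 2(N - 4) and lambda = f² x s x N.
- N = 45: df2 = 82, lambda = 0.16 x 2 x 45 = 14.40, power 0.790.
- N = 46: df2 = 84, lambda = 0.16 x 2 x 46 = 14.72, power 0.802.

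So 46 is the smallest N that reaches 80%. Other tests at f = 0.40 do not give 46: the between-factors test at correlation 0.5 gives 50, the univariate interaction 18, and the two-group version of the same test 64.

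**2. The same f(V) for one factor by time.** EC x time or tDCS x time has 2 df and s = 1, so lambda = 0.16 x N.
- N = 46: lambda = 7.36. Power is 0.646 with error df N - 3 = 43 (two-group model) and 0.644 with error df N - 5 = 41 (four-cell model).
- N = 64: lambda = 10.24, power 0.80. At N = 63 it is just below 0.80.

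**3. What the omnibus and a direct contrast detect.** Assumptions: N = 44 (55 x 0.8), 11 per arm, correlation 0.5 between visits (the document gives none), and the same effect at post and follow-up, in outcome SD. Each change score then has variance 1 and the two have covariance 0.5. For an EC-only effect d, the single non-zero root is (d²/4) x 2/1.5 = d²/3.
- d = 1.07: root 0.3816, V = 0.3816/1.3816 = 0.276, f(V) = sqrt(0.276/(2 - 0.276)) = 0.40. This matches the plan's effect size.
- d = 0.98 gives V = 0.2425 and f(V) = 0.37, slightly below it.

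Simulated rejection rates (20,000 trials per scenario); the EC contrast is the 1-df test on mean change over both later visits:

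| True pattern | Omnibus, 6 df | EC contrast, 1 df |
|---|---|---|
| EC only, 1.07 SD | 81% | 98% |
| EC and tDCS additive, 0.69 SD each | 72% | 73% |
| Only the combined arm moves, 1.2 SD | 78% | 61% |

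In the first row the tDCS and interaction contrasts reject in 5%, their null rate. In the second row the interaction contrast rejects in 5%. The omnibus result is the same kind of statement in all three rows. Part of the 98% comes from averaging the two later visits: the like-for-like 2-df EC x time test gives 95%.

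**4. Differences detectable at 80% power, N = 44, two-sided 0.05, unadjusted, in SD of the change score.** Detectable difference = delta x SE, where delta is the noncentrality that gives 80% power.
- Factorial margin, 22 v 22: SE = sqrt(2/22) = 0.302, delta = 2.87 (42 df), giving 0.86 SD.
- Arm v arm, 11 v 11: SE = sqrt(2/11) = 0.426, delta = 2.95 (20 df), giving 1.26 SD.
- EC x tDCS, (arm 1 - arm 2) - (arm 3 - arm 4): SE = sqrt(4/11) = 0.603, delta = 2.87 (40 df), giving 1.73 SD.

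**The case against.** The strongest reply is that a four-level arm factor is the same fitted model as EC, tDCS and EC x tDCS: all three effects are contrasts of it. Statistical analysis leaves room for other methods, and an article commonly leaves named contrasts to a SAP. This stands in part. A reader might infer that the plan can answer none of its three questions; the documents do not support that. The point is that the one analysis and the one sample size that are stated do not match the stated design and aims.

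Background also sets out to compare individual with combined interventions, and the trial is described as four-arm. So a four-arm comparison is one declared aim, and it would go too far to say that the 80% belongs to no hypothesis. It does not apply to EC, tDCS or boost taken separately.

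A reader might also infer that the omnibus test wastes power in general. It does not: it loses to the EC contrast when only EC works, about equals it for two additive effects, and rejects more often when only the combined arm moves. Nor does the article propose to compare the arms' significance levels. The wording in Expected outcomes is a loose expectation, not a test.

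Finally, that 46 was computed for the omnibus test is an inference from an exact match. Undocumented, non-default settings could change the between-factors alternatives.

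**Conclusion.** The mismatch holds. The design is a full 2x2 factorial with three separate questions, while the stated major analysis is a single arm by time test whose significance does not identify the source. The sample size of 46 matches that test exactly, at 80.2% power. If f(V) = 0.40 is meant for EC or tDCS by time, power at 46 is about 65%.

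The gain from direct contrasts is mainly in interpretation. The gain in power is clear only when one factor carries the effect (98% against 81% for EC alone at 1.07 SD). A factorial analysis also does not rescue the boost question: its detectable size, 1.73 SD, is twice that of a main effect. The simulated rates rest on an assumed visit correlation of 0.5, equal effects at both later visits and 44 evaluable patients.

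**What to change.** In Statistical analysis, replace the single arm factor with EC, tDCS and EC x tDCS, each by time, or list the equivalent contrasts. Test the boost by the interaction and report it as an estimate with a 95% confidence interval. If the expectation that the combination beats each component alone is kept, name the two comparisons it needs: arm 1 v arm 3 and arm 1 v arm 2. Which contrast is primary is the sponsor's choice; it should be fixed before analysis. If a boost is expected, the EC main effect averages two different EC effects, and that choice should take this into account.

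In Sample size, state that the 80% refers to the omnibus arm by time test, if that is confirmed. Give the power or detectable difference for each contrast, and say plainly that the interaction is underpowered.

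The cost is wording only: no extra patients, visits or data. The price is an open statement that the boost question can be estimated but hardly tested at this size.

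### Unless the four covariates are centred, the SPSS within-subject test of time refers to a person aged 0 with zero scores; the arm-by-time test is unaffected

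*Protocol article*

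**What the plan says.** All of the elements stand in the Statistical analysis section of the protocol article.

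- **Software.** Outcomes are to be "analyzed in detail using IBM SPSS statistics 25 for Windows".
- **Model and effects.** The main method is "mixed and repeated measures of multivariate analysis of variance (MANOVA) to assess the effect of group (arm) and time and their interactions", applied to EEG, computerised tests and self-report measures. Time is thus a named effect on every outcome family.
- **Covariates.** "The covariates, including age, disgust sensitivity, anxiety, and depression, will be considered in the statistical model". Neither raw nor centred entry is stated.
- **Level.** "The significant level will be set at 0.05".

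Three other places bear on the point. Participants sets the age range at 18 to 55 years. Self-report measures says that the DS-R, BAI and BDI-II are given only before treatment, so all four covariates are fixed values per person. Expected outcomes speaks of change over time, for instance on EEG: "we will look for changes in brain wave characteristics from pre- to post-interventions".

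**The concern.** In a repeated-measures general linear model with between-subject covariates, the differences between visits are regressed on arm and on each covariate. The within-subject test of time is the test of the intercept of that regression. An intercept is the expected change where every covariate equals zero.

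With raw covariates, that is the expected change in someone aged 0 with no disgust sensitivity, anxiety or depression. Nobody in the trial is near that point, so the estimate is an extrapolation with a large standard error. Two consequences follow for the time row. A real average change can come out non-significant. And if change varies with a covariate, the row can come out significant although the average change is nil.

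A report could then show arm means that clearly improve beside a time effect that is absent, or the reverse, and be misread on outcomes that include the primary ones.

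**Working it through.** **1. The plan's own figure.** Sample size assumes three measurements, "with 95% confidence and 80% power, estimating large effect size with Cohen’s" f of 0.40, and reports 46 participants. Taking the within-between interaction of a repeated-measures MANOVA (Pillai trace) with 4 arms and 3 visits:

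- s = min(3, 2) = 2; df1 = 3 × 2 = 6; df2 = 2 × (46 − 4) = 84
- λ = 0.40² × 2 × 46 = 14.72
- Power from the noncentral F is 0.802 at N = 46 and 0.790 at N = 45.

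So 46 reproduces exactly as the arm-by-time interaction. The version for the time factor gives 64.

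**2. Time test with centred covariates.** Assumptions: SD 1 at each visit, correlation 0.5 between visits, the same change d at post-treatment and follow-up, and covariates unrelated to change. The two differences from baseline each have variance 1 and covariance 0.5, so

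- λ = N × d² × 4/3 = 46 × 0.25 × 4/3 = 15.3 for d = 0.5
- Parameters: intercept, 3 arm terms, 4 covariates = 8; df = 2 and 46 − 8 − 1 = 37
- Power = 0.93.

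**3. Effect of raw entry.** The variance of the time estimate is multiplied by about V = 1 + μ′S⁻¹μ, where μ and S are the covariate means and covariance matrix. λ is divided by V.

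**4. A bound from the protocol alone.** For ages confined to 18–55, the squared ratio of mean to SD is at least 4 × 18 × 55 / 37² = 3960/1369 = 2.89. Hence V ≥ 3.89, and the standard error grows at least √3.89 = 1.97-fold. Power at 0.5 SD is at most 0.38. Adding further raw covariates can only raise V. If ages were uniform on 18–55, V = 1 + 36.5²/(37²/12) = 12.68, the standard error grows 3.56-fold and power is 0.14.

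**5. All four covariates.** The protocol gives no score means or SDs, so these are assumed ranges.

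| Assumed mean (SD): age; disgust; anxiety and depression each | Correlation among covariates | V |
|---|---|---|
| 33 (10); 50 (18); 14 (11) | 0 | 1 + 10.89 + 7.72 + 2 × 1.62 = 22.8 |
| same | 0.3 | 15.4 |
| 33 (8); 65 (12); 25 (9) | 0 | 1 + 17.02 + 29.34 + 2 × 7.72 = 62.8 |
| same | 0.3 | 37.9 |

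The standard error is therefore inflated about 3.9- to 7.9-fold. Simulated power of the time test at N = 46 (1,500 runs per setting):

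| True overall change | Raw | Centred |
|---|---|---|
| 0.5 SD | 0.06–0.12 | 0.92–0.93 |
| 0.8 SD | 0.08–0.23 | about 1.0 |
| 1.0 SD | 0.12–0.35 | about 1.0 |
| 1.5 SD | 0.18–0.64 | about 1.0 |

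The noncentral F with V from 15.4 to 62.8 gives 0.07 to 0.13 at 0.5 SD, in agreement.

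**6. False positives for time, no average change.**

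- Change unrelated to the covariates: raw 0.04–0.06, so no inflation.
- Change rising by 0.3 SD per SD of age: raw 0.17–0.30.
- Slopes of 0.2 SD per SD on all four in the same direction: raw 0.58–0.84.
- Centred, in the two settings with slopes: about 0.05–0.08.

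**7. Arm by time.** Centring moves only the intercept, not the arm terms. For an arm effect of 1 SD, rejection is 0.622 raw and 0.622 centred (2,000 runs). Under the null, both are about 0.05.

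**The case against.** The strongest objection is that raw entry is not in the text. The article says only that the covariates will be considered in the model. It is compatible with centred entry, or with a time effect taken from estimated marginal means. Coding of this kind is often left to an analysis plan, and none is shown here. This stands to the extent that the point must be put conditionally: a reader might infer that the protocol prescribes uncentred covariates, and it does not. What remains is that the article itself fixes the software, the model, the tested time effect and the covariates, and that this combination gives the wrong time test unless someone adds a step.

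The second objection is that the pooled time effect is not what the trial is about. The Background section and Expected outcomes compare separate with combined interventions against sham, and a change averaged over all four arms, double sham included, is no evidence of efficacy. This stands as well. A reader might infer that the trial's efficacy result is at risk. It is not, since the arm-by-time test is the same either way and is the test on which 46 was computed.

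Third, it would be tempting to say that a real change is almost always missed and that false time effects are to be expected. Neither holds in general. Even with raw covariates, a 1.5 SD change is found in 18 to 64% of runs. A false effect needs change to depend on a covariate, and nothing in the protocol says that it does.

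**Conclusion.** The point holds in limited form. Under the stated SPSS model, and unless the covariates are centred or time is read at their means, the within-subject time row does not describe patients aged 18 to 55.

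For a 0.5 SD overall change at N = 46, detection falls from about 93% to at most 38% on the age limits alone. It falls to roughly 6–12% under the assumed means and SDs for all four covariates. These figures also rest on a between-visit correlation of 0.5 and an equal change at both later visits. The loss shrinks as the true change grows.

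The effect is confined to the time main effect. The randomised comparison and the sample size stand. This is a free improvement to the plan, not a flaw in its main inference.

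**What to change.** Add one sentence to the Statistical analysis section: age, DS-R, BAI and BDI-II are centred at the whole-sample mean before entry in every repeated-measures model. Alternatively, state that the time effect is taken from estimated marginal means at the covariate means and not from the within-subject effects table. In either case, add that conclusions on efficacy rest on arm by time, and that the time effect is descriptive of the whole sample.

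The cost is that wording and a line of syntax. No further data or participants are needed, and no arm-by-time result changes.
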